## 1.2 FOOD ALLERGY

1.2.1 FOOD ALLERGY

Food allergy (FA) is defined as “a phenomenon in which adverse reactions are caused through antigen-specific immunological mechanisms after exposure to a given food” (27). FA is classified into two categories, namely, IgE-mediated FA and non-IgE mediated FA. IgE-mediated FA, which is more common than non-IgE mediated FA, causes allergic reactions within 2 hours and may cause anaphylaxis, which is life-threatening. Patients with IgE-mediated FA are sensitized to causal food, resulting in an elevation of food allergen-specific IgE titers. Although all patients who are sensitized to food allergens do not necessarily develop to adverse reactions to food allergens, the higher the IgE levels, the higher the risk of anaphylaxis. Patients with FA often have a lower quality of life as a result of restrictions on eating causal food, which is required because of their high risk of developing anaphylaxis (28).

1.2.2 FOOD ALLERGY EPIDEMIOLOGY

The prevalence of FA has been increasing worldwide (29). In Japan the most common causal allergen to FA was hen’s egg and the second most was cow’s milk (30). A hospital-based cohort study in Tokyo reported that the cumulative incidence of FA and hen’s egg allergy was 9% and 5.1%, respectively, among children aged 12 months (14). The prevalence of FA among children in elementary school has been increasing according to a national survey in Japan. The systematic review and meta-analysis demonstrated that cow’s milk and hen’s egg allergies were more common among younger children and the prevalence of food challenge-defined allergy to hen’s egg among 0–1-year-olds was 0.75% (0.46–1.04) among European populations (31). According to Table 3, the results of the prevalence of hen’s egg allergy showed large variations. The reason is considered to be that there are differences in diagnostic method for FA, definition, age, area, patients background, and so on.

Table 3. Observational studies of hen’s egg allergy and hen’s egg sensitization among infants

| Year, country, study design | Hen’s egg allergy | | | Hen’s egg sensitization | | |
| --- | --- | --- | --- | --- | --- | --- |
|  | All infants | With  eczema | Without  eczema | All infants | With  eczema | Without  eczema |
| 2007, Australia, cross-sectional (32) |  |  |  |  | 73% (34 w, 20-51 w) SPT  80% (34 w, 20-51 w) IgE |  |
| 2008, China, cross-sectional (33) |  |  |  |  | 70% (≤12 m) SPT |  |
| 2011, Sweden, cohort (34) |  |  |  | 24.8% (6 m) sIgE  32% (12 m) sIgE  27% (24 m) sIgE  51% (60 m) sIgE |  |  |
| 2011, Australia, cohort (35) | 8.9% (12 m) OFC |  |  | 16.5% (12 m) SPT≥1 mm  11.7% (12 m) SPT≥3 mm |  |  |
| 2012, Japan, cohort (36) |  |  |  |  | 87.5% (14 m) sIgE | 31.9% (14 m) sIgE |
| 2012, Iran, cross-sectional (37) |  |  |  |  | 17.7% (2-48 m) SPT |  |
| 2015, Australia, cohort (38) |  | 18.8% (12 m) OFC | 3.7% (12 m) OFC |  | 24.1% (12 m) SPT≥2 mm or sIgE≥0.35 | 5.2% (12 m) SPT≥2 mm or sIgE≥0.35 |
| 2016, Japan, cohort (14) | 5.2% (12 m)  questionnaire |  |  |  |  |  |

OFC, oral food challenge; SPT, skin prick test; sIgE, specific IgE titers; w, weeks of age; m, months of age

1.2.3 ATOPIC DERMATITIS AND SENSITIZATION THROUGH THE SKIN

Lack *et al.* demonstrated that peanut allergy was positively associated with the use of skin care products containing peanut oil in England (39). The results from the study suggested that peanut allergens absorbed through the skin may cause allergic sensitization. Van den Oord *et al.* demonstrated, in a systematic review and meta-analysis, that filaggrin gene defects among children increased the risk of developing allergic sensitization (OR 1.57; 95%CI: 1.20, 2.07) (40). Flohr *et al.* also showed that young infants with AD had an increased risk of allergic sensitization at the age of 3 months (aOR 6.18; 95%CI: 2.94, 12.98; *p*<0.001) (41). Spergel *et al.* showed that total serum IgE and serum egg white-specific IgE in a cohort study increased in patients with increased AD severity (42). From a review of past studies (Table 3), the prevalence of hen’s egg allergy or hen’s egg sensitization in infants varies depending on various characteristics such as with/without eczema, timing of hen’s egg introduction, country, age, and diagnostic method for FA and infants with eczema tend to have higher prevalence of IgE sensitization than those without eczema.

1.2.4 ATOPIC DERMATITIS AND FOOD ALLERGY

Martin *et al.* reported that 20% of 1-year-old infants who had a history of eczema received a diagnosis of FA (38). Additionally, 50.8% of infants (95%CI: 42.8, 58.9) with early eczema onset (<3 months old) who required doctor-prescribed topical corticosteroid treatment developed challenge-proven FA. Shoda *et al.* demonstrated that in each age (by month) stratum, infants with onset of eczema within the first 1–2 months after birth had the highest risk of FA at 3 years of age (aOR 6.61; 95%CI: 3.27, 13.34; *p*<0.001) and the second highest was within 3–4 months after birth (aOR 4.69; 95%CI: 2.17, 10.13) (14). The results from previous studies suggest that infants who develop AD in early infancy have a higher risk for FA. We summarize the prevalence of hen’s egg sensitization among patients with AD in Table 3.

1.2.5 ORAL TOLERANCE

Oral tolerance is defined as a state of suppression or non-reactivity towards immunological response to oral allergen exposures from eating the allergenic food. The gastrointestinal mucosa is exposed to a wide variety of antigens, but most of food-derived antigens are not harmful to humans. This is because humans have an antigen recognition mechanism for inducing immune tolerance, not for providing unnecessary immune response against food antigens (27). However, Du Toit *et al.* reported that Jewish children in the UK had a 10-fold higher prevalence of peanut allergy than Jewish children in Israel (43). The major explanation was that there is a difference in dietary habits between the UK and Israel. It was suggested that the possibility that the parents of children in Israel do not restrict intake of peanuts during infancy, whereas parents in the UK limit intake of peanuts during infancy (Du Toit *et al.*). Du Toit and colleagues conducted a randomized controlled trial (LEAP Study) to examine the prevention of peanut allergy by early peanut ingestion in 640 infants with atopic dermatitis and egg allergy (44). Infants in the consumption group who initially had negative results on the skin-prick test started taking peanuts when they were at least 4 months old and less than 11 months old at randomization. The prevalence of peanut allergy in the avoidance group at 60 months of age was significantly higher than that in the consumption group (13.7% vs. 1.9%; *p*<0.001). The findings supported the past results of epidemiological studies in Jews.

Perkin *et al.* conducted an RCT (EAT Study) that examined whether infants in the general population can prevent the onset of food allergy at 3 years old by regularly consuming allergenic foods such as hen’s eggs from 3–4 months after birth. Regarding hen’s eggs, the early consumption group (n=569) was to take ½ of a heated hen’s egg twice a week from 3–4 months after birth periodically according to the study, but only 215 participants could take heated hen’s egg according to the study protocol. The prevalence of hen’s egg allergy was 3.7% in the early consumption group (n=569) and 5.4% in the standard consumption group (n=596) by the Intention to Treat (ITT) analysis, and 1.4% in the early consumption group (n=215) and 5.5% in the standard consumption group (n=525) by the Per Protocol (PP) analysis. There was no significant difference in the prevalence of hen’s egg allergy between both groups in the ITT analysis (45). Bellach *et al.* conducted an RCT (HEAP Study) to investigate the efficacy and safety of early hen’s egg introduction at age 4–6 months to prevent hen’s egg allergy in the general population (46). The early consumption group took egg white powder (equivalent to ⅓ of a hen’s egg) three times per week from 4–6 months old to 12 months, while the placebo group eliminated hen’s egg and took rice flour three times per week from 4–6 months old to 12 months. The prevalence of egg allergy among the participants at 12 months of age in the HEAP Study was 2.1% in the early consumption group (n=142) and 0.6% in the placebo group (n=156) (relative risk 3.30; 95%CI: 0.35, 31.32).

Palmer *et al.* also performed an RCT (STEP Study) to examine if regular egg protein consumption from 4–6 months of age reduces a risk of IgE-mediated hen’s egg allergy in high-risk infants without eczema (47). The early consumption group took 0.9 g of pasteurized raw hen’s egg powder every day from 4-6 months old to 10 months after birth (equivalent to ½ of a whole egg in one week), and the placebo group took powder without hen’s egg every day from 4-6 months old to 10 months and eliminated hen’s egg. The prevalence of IgE-mediated hen’s egg allergy at the age of 12 months was 7.0% in the early consumption group (n=407) and 10.3% in the placebo group (n=413) (adjusted relative risk 0.75; 95%CI: 0.48, 1.17), but did not show a statistically significant difference. On the other hand, Natsume *et al.* conducted a double-blind, placebo-controlled RCT (PETIT Study) for infants 4–5 months of age with eczema who were enrolled and randomly assigned to the early introduction of egg or placebo to examine the proportion of participants with hen’s egg allergy confirmed by open oral food challenges at 12 months of age (48). Participants in the early egg consumption group consumed 0.2 g of heated hen’s egg every day during 6–8 months of age and 1.1 g of heated hen’s egg every day during 9–12 months of age. The participants’ eczema was aggressively treated at entry and skin conditions of most participants were maintained without exacerbations throughout the intervention period. In the study, 121 participants revealed that the prevalence of egg allergy was 37.7% in the placebo group (n=61) and 8.3% in the egg group (n=60), and the risk ratio was 0.221 (95%CI: 0.090, 0.543; *p*=0.00013); this demonstrated that the prevalence in the egg group was significantly lower than that in the placebo group. The results among these three RCTs were different and the reasons were considered to be different background of participants (high risk infants, or general infants), race, method of egg consumption, eczema control level, and so on. Immune tolerance is not considered to be induced merely by orally taking allergenic foods from the early stage of infancy.

1.2.6 Dual-allergen-exposure hypothesis

Lack *et al.* suggested the dual-allergen-exposure hypothesis which states that tolerance is induced from oral exposure to food antigen, enhancing immune response to suppress allergy and that infants with eczema are exposed to food antigen via skin and induce immune cells, enhancing allergy and producing IgE antibodies (sensitization) (Fig. 3) (49). This hypothesis implies that it is important not only to induce oral immune tolerance, but to prevent allergic sensitization through the skin to reduce allergies.

Figure 3. Dual-allergen-exposure hypothesis (49)

1.2.7 TREATMENT FOR FOOD ALLERGY

FA treatment is basically the minimum necessary food elimination based on correct diagnosis. We should ensure safety (50). In the level of clinical studies, several clinical trials have been conducted to evaluate the efficacy and safety of immunotherapy, inducing immune tolerance (51). Caminiti *et al.* performed an RCT regarding oral immunotherapy of hen’s egg for children with hen’s egg allergy (52). The patients who received 4-month oral immunotherapy (n=16/17) were desensitized to hen’s egg compared to patients in the placebo group who were not desensitized (n=0/14). However, when OFC of hen’s egg was conducted after elimination of hen’s egg for 3 months after continuing taking hen’s egg for 10 months from the initial intervention, 31% (5/17 people) showed symptoms for hen’s egg allergy again. It was suggested that food allergy reactions might be induced for hen’s egg if hen’s egg is eliminated for a long period of time. Oral immunotherapy for food allergy is still at the research level and is not recommended as clinical practice in the food allergy guidelines not only in Japan, but also in Europe and the United States. In the future, development of oral immunotherapy as a treatment for food allergy will be expected to be available to induce immune tolerance for causal food allergen and to be applied to daily clinical practice.

## 1.3 EXPECTATIONS FOR EARLY AGGRESSIVE INTERVENTION FOR ATOPIC DERMATITIS

Allergic march refers to the natural history or typical progression of allergic diseases that often begin early in life. These include AD (eczema), FA, allergic rhinitis (hay fever), and asthma (53). In most patients, AD is the first clinical manifestation with the highest incidence in the first year of life and those affected develop other allergic diseases such as FA, asthma, and allergic rhinitis later in childhood. We hypothesize that to prevent future allergic march, an appropriate intervention for AD, which emerges at the first stage of allergic march, is important to be considered. We expect that early aggressive intervention for AD will likely prevent development of later allergen sensitization, FA, asthma, and allergic rhinitis.

## 1.4 NECESSITY AND SIGNIFICANCE OF THE STUDY

Shoda *et al.* demonstrated that in each age (by month) stratum, infants with onset of eczema within the first 1–2 months after birth had the highest risk of FA at 3 years of age (aOR 6.61; 95%CI: 3.27, 13.34; *p*<0.001) and the second highest was within 3–4 months after birth (aOR 4.69; 95%CI: 2.17, 10.13) (14). Infants who develop AD in early infancy have a high risk of developing FA. The increasing prevalence of FA is a current worldwide epidemic. According to the national survey by the ministry of education, culture, sports, science and technology, the percentage of school children with past history of anaphylaxis was 0.14% in 2004 and 0.5% in 2013, an increase of nearly 4 times (54). As we mentioned before, we think that it is important to introduce oral immune tolerance by early hen’s egg consumption and prevent sensitization via skin to prevent the development of food allergy. To our knowledge, this would be the first RCT study to examine the efficacy of early aggressive intervention for AD to prevent later FA. If we establish a novel new strategy for prevention of FA development by early aggressive intervention for AD, it is expected that quality of life in patients will improve, the prevalence of FA will decrease, and the medical care cost will be reduced.

# 2 PURPOSE

The purpose is to test by a randomized controlled trial the superiority of aggressive intervention over conventional treatment of infantile atopic dermatitis (AD) to prevent food allergy.

## 2.1 STUDY HYPHOTHESIS

Aggressive intervention is superior to conventional treatment to prevent the development of IgE-mediated hen’s egg allergy.

# 3 DEFINITIONS

**Atopic dermatitis (AD)** In this study, we use the U.K. Working Party’s diagnostic criteria for AD (55-57). The U.K. Working Party’s diagnostic criteria were validated as diagnostic criteria for AD by Williams *et al.* AD is a diagnosis with one major criterion plus three or more minor criteria in the U.K. Working Party’s diagnostic criteria (Table 4).

Table 4. The U.K. Working Party’s diagnostic criteria

| Major criterion |
| --- |
| An itchy skin condition (or parental report of scratching or rubbing in a child) |
| Minor criteria |
| History of involvement of the skin creases such as folds of elbows, behind the knees, front of ankles, or around the neck (including cheeks in children under 10). |
| A personal history of asthma or hay fever (or history of atopic disease in a first-degree relative in children under 4). |
| A personal history of general dry skin in the last 12 months. |
| Visible flexural eczema (or eczema involving the cheeks/forehead and outer limbs in children under 4. |
| Onset under the age of 2 (not used if child is under 4). |

**Skin rash severity** The definition of severity for skin rash is taken from the clinical practice Guidelines for the Management of Atopic Dermatitis (2016) (1), which are listed below (Table 5).

Table 5. Skin rash severity

| Skin rash severity | Cutaneous manifestations |
| --- | --- |
| Less mild | Primarily dryness with negligible inflammation |
| Mild | Primarily dryness, mild erythema and scales |
| Moderate | Primarily moderate erythema, scales, a few papules and excoriations |
| Severe | Primarily severe swelling/edema/infiltration or erythema with lichenification, multiple papules, severe scales, crusts, vesicles, erosion, multiple excoriations and pruriginous nodules |

**Disease-free day** Condition without skin rash caused by AD on any area of the body.

**Degree of rescue treatment for atopic dermatitis during the study**

The amount of applied Fulumeta^®^ ointment is used as the evaluation of the degree of rescue treatment.

**Infants’ Dermatitis Quality of Life Questionnaire (IDQoL)**

IDQoL was developed by Lewis-Jones *et al*. as an evaluation scale of QoL for infants under 4 years old with atopic dermatitis (58, 59).

**Family Impact of Childhood Eczema Questionnaire (DFI)**

DFI was developed by Lawson *et al*. as an evaluation scale of QoL for the family members who have a child with atopic

dermatitis (60). Parents answer the questionnaire.

**EASI (Eczema Area and Severity Index)** The EASI score, developed by Hanifin *et al.*, is a tool used to measure the extent (area) and severity of atopic eczema (Eczema Area and Severity Index) (61). In this study, a medical doctor evaluates the eczema region, extent (area) and severity of eczema, and calculates an EASI score. EASI has been recommended as an outcome measure for AD in clinical trials by the global Harmonising Outcome Measures for Eczema (HOME) (62).

**POEM (Patient Oriented Eczema Measure)** The POEM score, developed in 2004 by Williams *et al*., is a tool used to measure severity of AD by patients (caregivers) (63). The POEM questionnaire consists of 7 questions evaluating skin dryness, skin redness, sleep disturbance, and so forth, due to AD. Caregivers answer the questionnaire once a week and severity of AD is evaluated by the POEM score. POEM has been recommended as an outcome measure for AD by caregivers in the HOME (64).

One finger-tip unit (FTU)

One FTU describes the amount of cream squeezed out of its tube onto the end of the finger, which is almost equal to 0.5 g of cream. One FTU is enough to treat an area of skin twice the size of the flat palmar surface of an adults’ hand with fingers together (17).

**IgE-mediated hen’s egg allergy proven by the oral food challenge test (OFC)**

A positive open hen’s egg challenge test at the age of 28 weeks is assessed by a blinded physician (see 6.2). Following the PRRACTALL criteria in Table 6 (65), the challenge tests are scored as positive if participants meet any of the three criteria below within 2 hours after last ingesting hen’s egg:

1. One or more [A] scoring areas
2. Three or more [B] scoring areas
3. Persistence of one or more [B] scoring areas

Table 6. Scoring the challenge outcome (PRRACTALL criteria) (65)

| Ⅰ.  Skin | A. Erythematous rash: % area involved (see body surface area diagram), using rule of five.  0 = Absent  1 = Mild, few areas of faint erythema / 1-3 spots, 5-10％  2 = Moderate areas of erythema / >10%, ≤50%  3 = Severe generalized marked erythema / >50%  Figure 4. Rule of five  [figure not shown] | |
| --- | --- | --- |
|  | B. Pruritus | 0 = Absent |
|  |  | 1 = Mild, occasional scratching |
|  |  | 2 = Moderate: scratching continuously for >2 minutes at a time |
|  |  | 3 = Severe: hard continuous scratching, excoriations [B] |
|  | C. Urticaria / angioedema | 0 = Absent |
|  |  | 1 = Mild: less than 3 hives, or mild lip edema [B] |
|  |  | 2 = Moderate: more than 3 and less than 10 hives, or significant lip or face edema [A] |
|  |  | 3 = Severe: generalized involvement [A] |
|  | D. Rash | 0 = Absent |
|  |  | 1 = Mild: few areas of faint erythema |
|  |  | 2 = Moderate: areas of erythema [B] |
|  |  | 3 = Severe: generalized marked erythema (>50%) [A] |
| Ⅱ. Upper respiratory | A. Sneezing/ Itching | 0 = Absent |
|  |  | 1 = Mild: rare bursts, occasional sniffling |
|  |  | 2 = Moderate: bursts <10, intermittent rubbing of nose and/or eyes or frequent sniffling [B] |
|  |  | 3 = Severe: continuous rubbing of nose and/or eyes, periocular swelling and/or long bursts of sneezing, persistent rhinorrhea [A] |
| Ⅲ.  Lower respiratory | A. Wheezing | 0 = Absent |
|  |  | 1 = Mild: expiratory wheezing on auscultation [A] |
|  |  | 2 = Moderate: inspiratory and expiratory wheezing [A] |
|  |  | 3 = Severe: use of accessory muscles, audible wheezing [A] |
|  | B. Laryngeal | 0 = Absent |
|  |  | 1 = Mild: >3 discrete episodes of throat clearing or cough, or persistent throat tightness/pain [B] |
|  |  | 2 = Moderate: hoarseness, frequent dry cough [A] |
|  |  | 3 = Severe: stridor [A] |
| Ⅳ.  Gastrointestinal | A. Subjective Complaints | 0 = Absent |
|  |  | 1 = Mild: complaints of nausea or abdominal pain, itchy mouth/throat [B] |
|  |  | 2 = Moderate: frequent complaints of nausea or pain with normal activity [B] |
|  |  | 3 = Severe: notably distressed due to GI symptoms with decreased activity [B] |
|  | B. Objective Complaints | 0 = Absent |
|  |  | 1 = Mild: 1 episode of emesis or diarrhea [B] |
|  |  | 2 = Moderate: 2-3 episodes of emesis or diarrhea or 1 of each [A] |
|  |  | 3 = Severe: >3 episodes of emesis or diarrhea or 2 of each [A] |
| Ⅴ.  Cardiovascular |  | 0 = Absent: normal heart rate and/or blood pressure for age or patient’s baseline |
|  |  | 1 = Mild: subjective response (weak, dizzy), or tachycardia [B] |
|  |  | 2 = Moderate: drop in blood pressure and/or >20% from baseline, or significant change in mental status [A] |
|  |  | 3 = Severe: cardiovascular collapse, signs of impaired circulation (unconsciousness) [A] |

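### The primary-endpoint challenge rule scores skin signs as absolute levels after egg, without a pre-dose comparison, so residual eczema could count as egg allergy more often in the conventional arm

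*Protocol*

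**What the plan says.** The endpoint is defined in Protocol section 3, under the entry for egg allergy proven by oral food challenge (OFC): "the challenge tests are scored as positive if participants meet any of the three criteria below within 2 hours after last ingesting" hen's egg. The three criteria are "One or more [A] scoring areas", three or more [B] areas, and "Persistence of one or more [B] scoring areas".

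In the skin block of Table 6, two items matter here:

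- Rash (item D): grade 2 is "2 = Moderate: areas of erythema [B"], and grade 3 is "3 = Severe: generalized marked erythema (>50%) [A"].
- Pruritus (item B): grade 3 is "3 = Severe: hard continuous scratching, excoriations [B"].

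Neither item says that the sign must be new or worse than before the egg. The same table does use a reference state for cardiovascular signs: "2 = Moderate: drop in blood pressure and/or >20% from baseline, or significant change in mental status [A"].

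Table 5 of the same section describes a moderate atopic dermatitis rash as "Primarily moderate erythema, scales, a few papules and excoriations".

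Section 6.2 gives the challenge material, the three dose steps and the interval. It mentions no skin score before the first dose, no condition on the state of the skin and no placebo step. Section 5.4 blinds the physicians who perform the challenge and examine the skin. Sections 6.1 and 6.2 schedule a blinded EASI and specific IgE at the 28-week visit, but do not link either to the challenge result.

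**The concern.** The signs that earn a [B] or an [A] under rash and pruritus are also signs of active atopic dermatitis, the disease that every participant has (section 4.1). Eczema present on arrival is likely to be there still two hours after the last dose, so it readily fits the persistence criterion. The arms differ in their dermatitis treatment up to 28 weeks of age (sections 5.6.3 and 5.6.4). Section 1.1.3 cites a randomized trial in which proactive treatment lowered the severity score relative to reactive treatment. Residual eczema is therefore expected more often in the conventional arm, and misscoring would favour the aggressive arm.

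Blinding stops the assessor from scoring by arm. It does not change what is on the skin. At stake is whether a lower rate of challenge-proven egg allergy reflects less allergy or, in part, clearer skin.

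**Working it through.** **The text.** Three checks decide whether the printed rule can count pre-existing eczema.

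1. *Is there a reference state for skin?* No. Table 6 refers to a baseline only in the cardiovascular block.
2. *Can a single skin item decide the result?* Yes. Rash grade 2, or pruritus grade 3, is one [B], and if it persists the third criterion is met. Rash grade 3 is one [A] and meets the first. The separate erythema-area item (skin item A) carries no letter, so the route runs through items B and D only.
3. *Does anything else screen such a case out?* No. The definition asks for no egg-specific IgE. The justification of the open challenge in section 8.1 deals with subjective and psychogenic reactions, not with eczema.

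**The design figures.** The plan gives no figure for misscoring. Its design inputs (section 9.1: 20% v 30%, one-sided 0.025, 80% power) reproduce. The unpooled formula gives (1.960 + 0.842)² × (0.30×0.70 + 0.20×0.80) / 0.10² = 290.4, so 291 per arm and 582 in total, against the stated 581. The point below does not alter 581, 614 or 650.

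**Size under assumptions.** Let π be the true allergy rate, e the share of infants with scorable eczema at the challenge, and q the chance that a non-allergic infant with such eczema is scored positive. Then:

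observed rate = π + (1 − π) × e × q

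Assume no true effect: π = 0.25 in both arms, the midpoint of the two design rates. Take 325 per arm (section 0.7) and a fixed-sample one-sided test at 0.025, ignoring the interim. The chance of rejection is 1 − Φ(1.960 − Δ/SE). Here Δ is the spurious difference and SE its standard error, about 0.034 to 0.035. None of the values of e and q comes from the documents.

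| e, aggressive v conventional | q | Observed rates | Δ (points) | One-sided type I error |
|---|---|---|---|---|
| 10% v 30% | 2% | 25.15% v 25.45% | 0.3 | 0.031 |
| 5% v 10% | 10% | 25.375% v 25.75% | 0.4 | 0.032 |
| 10% v 30% | 10% | 25.75% v 27.25% | 1.5 | 0.063 |
| 10% v 30% | 20% | 26.5% v 29.5% | 3.0 | 0.134 |

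Example, third row: 0.25 + 0.75×0.10×0.10 = 0.2575 and 0.25 + 0.75×0.30×0.10 = 0.2725. Then Δ/SE = 0.015/0.0346 = 0.433, and 1 − Φ(1.527) = 0.063.

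For misscoring alone to produce the whole 10-point design effect, e × q would have to differ between arms by 0.10/0.75 = 13.3 points. With shares of 10% v 30% that needs q = 0.133/0.20 = 67%.

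If misscoring were equal in both arms, it would dilute a true effect. With true rates of 30% v 20% and 10% of non-allergic infants misscored, the observed rates are 37% v 28%. The difference is then 9 points, and power at 307 per arm falls from 0.82 to 0.66.

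**The case against.** The strongest reply is that Table 6 scores the outcome of a challenge, and that section 1.2.1 defines food allergy as an adverse reaction following exposure to the food. In that light a persistent [B] means a provoked sign that does not fade, and a sensible blinded physician would discount old rash. The protocol also adopts its criteria from a cited consensus report, whose rules on pre-challenge assessment cannot be seen here. This makes large-scale misscoring less likely. It does not change the rule that the protocol prints, and unwritten discounting may vary between sites.

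Three further points reduce the likely size:

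- The letters start high. Mild and moderate pruritus and mild rash carry none.
- The conventional arm is not untreated. It receives daily topical steroid for mild rash or worse, a stronger preparation if rash persists, and a possible switch of regimen after 8 weeks (section 5.6.4).
- A blinded EASI is scored at the same visit, so positives can be compared with skin state in both arms. Its timing relative to the challenge is not given.

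There is also a fair objection to the remedy: requiring a new or increased sign can hide a true skin reaction in an infant who arrives with marked erythema. By the argument made here, such infants are more often in the conventional arm, so the stricter rule could err the other way.

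A reader might infer that the endpoint will show fewer egg allergies merely because eczema is better controlled, or that type I error is at least doubled. The documents support neither. They give no eczema share at the challenge and no misscoring rate, and plausible low values leave the error close to 0.03.

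**Conclusion.** The point stands as a gap in the definition of the primary endpoint. Followed literally, the rule can count residual eczema as egg allergy. The expected direction favours the aggressive arm, and blinding does not correct it.

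The size cannot be derived from the documents. Under the assumptions stated (no true effect, 25% in both arms, 325 per arm, interim ignored), one-sided type I error runs from about 0.03, for instance with 10% v 30% eczema and 2% misscored, to 0.06 and 0.13 with 10% and 20% misscored. These are illustrations, not bounds. The calculation also leaves out the rule in section 9.3.2 that counts missing outcomes as allergic. The definition should be changed because it governs the primary comparison and is cheap to correct, not because a large bias has been shown.

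**What to change.** 1. In the section 3 definition and the challenge procedure in section 6.2, have the blinded physician record the Table 6 skin items immediately before the first dose. State that a skin item counts towards a positive only if it is new or has increased in grade after a dose. This concerns scoring of the endpoint only.
2. Add a sensitivity analysis in which a positive also needs egg-white-specific IgE of at least 0.35 UA/mL. That is the protocol's own sensitization threshold (section 3), and the test is already scheduled at this visit (section 6.1).
3. Report the primary comparison under the rule as now printed as well, and give by arm the number of positives that rest on eczema-like skin items alone.

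The cost is a sentence in the definition, a pre-dose column on the challenge form and two supplementary tabulations. Slightly fewer positives are to be expected, and true skin reactions may be masked in infants with a high pre-dose score. Item 3 is there to make that visible.
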